### Treatment integrity

Clinical psychologists will deliver the intervention. Fidelity and clinical adherence will be established through continued monitoring and independent rating. Specifically, clinicians will complete a modified version of the Therapist Fidelity Checklist (TFC; [26]), which is a session-by-session measure of compliance with the protocol, and these will be evaluated during weekly clinical supervision. In addition, treatment sessions will be video-taped and all assessments audio-taped. A random sample of 20% of recordings will be reviewed by the lead developer of TF-CBT (PS), who is not involved in day-to-day running of the trial.

### Measures

#### Primary clinical outcomes

The primary outcome will be recovery from PTSD using the DIPA at post-treatment. The DIPA is a psychometrically robust parental report semi-structured interview designed for this age group [19].

### Secondary clinical outcomes

As secondary outcomes, DIPA PTSD at 3-month and 12-month follow-ups, effects on co-morbid diagnoses (assessed with the DIPA) and changes on the parent-completed Young Child PTSD Checklist [26], the Pediatric Emotional Distress Scale (PEDS; [27]), and the Preschool Feelings Checklist (PFC: [28]), will be evaluated. These questionnaire measures provide continuous assessment of psychological symptoms of PTSD symptoms, general distress, and emotion functioning, respectively. Participants across both trial arms complete these questionnaires at baseline and post-treatment, with the trial arm also completing the measures at 3-months and 12-months post-treatment.

### Additional outcomes

Broader efficacy will be considered with regard to treatment outcome, treatment acceptability, and cost-effectiveness. Data to assess these additional outcomes will include qualitative, quantitative and health economics data as detailed below.

### Semi-structured interviews

Treatment outcome will be evaluated using quantitative measurement of potential PTSD symptom reduction from pre- and post-treatment as noted above, as well as an embedded qualitative study to elicit parents’ and children’s lived experiences of treatment. Semi-structured interviews will be conducted with a small sub-section (n ≈ 15) of those involved at different stages of the trial; specifically, treatment completers, treatment non-completers, treatment non-consenters and those who went from TAU to TF-CBT-YC. The aim is to garner the views of those who received treatment, either immediately, or after TAU. The views of those who did not consent or withdrew from the trial will also be sought to help us to understand the reasons for this. Interviews will cover topics that include: parents’ and children’s experience of the assessment process; treatment sessions; homework tasks; the practicalities of receiving treatment and perceived treatment impact. They will be conducted at 3 months post-treatment, or at 3 months following withdrawal from the study. It is acknowledged that this may be difficult in the case of those withdrawing or not consenting to be part of the study and, therefore, interviews may be conducted earlier as appropriate. Interviews will be conducted face-to-face, unless a participant declines, at which point a telephone interview will be offered.

### Additional quantitative measures

Feasibility and acceptability of the intervention will be assessed through a mixture of quantitative and qualitative methods. The feasibility and acceptability of TF-CBT-YC will be examined in three ways. First, a modified version of the clinician-completed Adaptability Checklist-Child (ACC16; [26]) will be used, which is a quantitative feasibility measure of the child’s ability to engage with and benefit from the different components of TF-CBT-YC (also used in the previous trial conducted in the USA, [17]). Second, treatment credibility items and the Therapeutic Alliance Scale [29,30] will be completed by parents or carers with their child’s input, at mid-treatment and post-treatment, to give an overview of the acceptability of the treatment to the child and their parents or carers. Third, a semi-structured interview as described above examines aspects of treatment feasibility and acceptability.

### Health economics measures

Data collection for the health economic evaluation will take a broad societal perspective, recording all hospital, community health and social services usage. Productivity losses resulting from time off work by parents or carers as a consequence of their child’s PTSD will be calculated using the human capital approach, a multiplication of days off work due to illness by the individual’s salary level [31]. Data will be collected using a structured questionnaire adapted for this study but based on the Child and Adolescent Service Use Schedule (CASUS), an instrument previously used in a trial of CBT for major depressive disorder in adolescents [32]. Data on TF-CBT-YC contact time and on indirect time (for example, supervision) spent delivering the intervention will also be collected. Cost information will be taken from national publications. Together, these data will allow us to test our resource utilisation instruments and permit preliminary estimates of TF-CBT-YC’s potential cost-effectiveness.

### Methodological aspects

#### Data collection

Quantitative outcome variable data for the trial will be collected at baseline, post-treatment, 3-month and 12-month follow-up. Qualitative interview data on treatment completers will be collected at 3-month follow-up, except in the case of participants who drop out earlier who will be followed-up as appropriate. Health economics data will be collected retrospectively (for the preceding 3-months) at all 4 assessment time points.

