## Methods/Design

### Study design

This study is a two-arm pilot randomised controlled trial (RCT) comparing TF-CBT-YC with treatment as usual (TAU). A half-crossover design will be employed such that participants allocated to the TAU arm will be offered the intervention after a 12-week waiting period if still indicated. Participants will be assessed 4 times during the study - at baseline, at post-TAU or -treatment, and at 3-month and 12-month follow-up for participants allocated to the treatment condition (see Figure 1). The post-treatment assessment will be conducted in the week following treatment completion and the post-TAU assessments will be at a comparable duration in the TAU arm.

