## Discussion

PTSD is a distressing and debilitating mental health condition. If left undiagnosed and untreated, PTSD can take a chronic course and lead to significant functional impairment [13]. TF-CBT is an evidence-based treatment with demonstrated efficacy for older children, adolescents and adults [25]. However, there is no evidence base for its efficacy in younger children. There has been a growing recognition of the need to develop an age appropriate treatment model for younger children; this exploratory RCT meets this objective. The timely nature of this trial is underscored by the inclusion of a preschool age criteria included in the recent DSM-5, reflecting the growing recognition that PTSD in this age group needs to be addressed.

Data evaluating the effectiveness of TF-CBT-YC will provide an initial step towards providing an empirical base for the treatment of young children with PTSD. If superiority to TAU can be demonstrated, the results from this trial will support the need for a fully powered definitive trial to examine TF-CBT-YC as the treatment of choice for young children with PTSD. Not only is this trial needed to examine efficacy, feasibility and acceptability, but the economic evaluation of this treatment will determine its cost-effectiveness over the medium to long term and, therefore, TF-CBT-YC’s applicability to delivery through NHS channels. Accordingly, TF-CBT-YC has the potential to bring benefits to young children affected by PTSD, but also to the health system more broadly.

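### A fixed 3-month recall leaves service use in months 3 to 9 after treatment unobserved in the treatment arm, and the Discussion claims more than the economic data can show

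*Protocol article*

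**What the plan says.** The Data collection section fixes both the recall period and the occasions: "Health economics data will be collected retrospectively (for the preceding 3-months) at all 4 assessment time points". The same section gives the schedule: "Quantitative outcome variable data for the trial will be collected at baseline, post-treatment, 3-month and 12-month follow-up". Under Secondary clinical outcomes the two follow-ups are counted from the end of treatment, "with the trial arm also completing the measures at 3-months and 12-months post-treatment". Study design places the preceding visit close to that point: "The post-treatment assessment will be conducted in the week following treatment completion".

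Study design also limits the later visits to one arm, "at 3-month and 12-month follow-up for participants allocated to the treatment condition", and says that children allocated to TAU "will be offered the intervention after a 12-week waiting period if still indicated".

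The economic aims are stated at different strengths:

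- Health economics measures intends to capture every hospital, community and social service contact and parents' lost work time, but describes the product as a test of the instruments and preliminary estimates.
- Background makes a possible NHS saving in overall post-trauma service costs one of the three main questions.
- The Discussion goes furthest: "the economic evaluation of this treatment will determine its cost-effectiveness over the medium to long term".

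**The concern.** A 3-month recall covers the time between visits only when the visits are no more than 3 months apart. The last two are 9 months apart. Service use that nobody asks about cannot be recovered in the analysis, and the article mentions no diary, record extraction or interim contact that would supply it. The look-back is a stated design choice, so a statistical analysis plan could not repair it.

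At stake is the 12-month cost profile of treated children. A total over follow-up would need either a sum with a half-year hole in it or an interpolation that the article does not describe. Parental work loss has the same gap if, as the text suggests, it comes from the same questionnaire.

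**Working it through.** The article gives no coverage figure to reproduce, so the check is interval arithmetic on its own schedule.

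**Inputs.** Let T be the time from baseline to the post-treatment visit. Study design gives a 12-week period and an assessment in the week after treatment ends, so T is 12 to 13 weeks: 12 × 7 / 30.4375 = 2.76 months to 13 × 7 / 30.4375 = 2.99 months. The visits are at 0, T, T + 3 and T + 12 months. Each recall window runs from 3 months before the visit to the visit.

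**Windows in months relative to the post-treatment visit, with T = 3.**

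| Visit | Window covered |
|---|---|
| Baseline | −6 to −3 (before randomisation) |
| Post-treatment | −3 to 0 |
| 3-month follow-up | 0 to +3 |
| 12-month follow-up | +9 to +12 |

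**Gap.** Months +3 to +9 are in no window. The gap is (12 − 3) − 3 = 6 months, whatever the value of T.

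- Share of post-treatment time: 6 / 12 = 50%.
- Share of time from baseline, T = 3: 6 / 15 = 40%.
- Share of time from baseline, T = 2.76: 6 / 14.76 = 40.7%.

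**Between-arm comparison.** The primary outcome is measured at post-treatment. The Statistical analysis plan section bases its primary cost-effectiveness analysis on loss of the PTSD diagnosis and calculates an incremental ratio only if the primary outcome differs. With T between 2.76 and 2.99 months, the 3-month recall at the post-treatment or post-TAU visit covers the whole randomised period. Therapist contact and supervision time is collected separately and is not affected.

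If T were 4 months, which is an assumption because the article gives no figure for overruns, the first 4 − 3 = 1 month of treatment would also be missed.

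**What 50% means.** Suppose use is constant at r per month. The true post-treatment total is 12r.

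- The recall windows observe 3r + 3r = 6r, so a plain sum would be half the truth.
- Filling the gap at the observed rate adds 6r and gives 12r, with no bias.
- If the monthly rate in the gap differs from the observed rate by d, the filled total is wrong by 6d.

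The article plans neither the sum nor the filling, so 50% measures missing observation only.

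**After the change.** A 9-month recall at the 12-month visit covers +3 to +12, and the uncovered time falls from 6 of 12 months to 0 of 12. TAU children still have no cost data after their post-TAU visit.

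**The case against.** The strongest reply is that the planned economic comparison does not use the missing months. It compares the two arms and rests on an outcome at post-treatment, and that period is covered. This stands.

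Two stronger readings are therefore tempting but not supported:

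- A reader might infer that the trial's cost estimates will be too low by half. That would hold only for a plain sum of post-treatment windows under a constant rate of use, and no section plans such a sum.
- A reader might infer that a longer recall would deliver the long-term answer promised in the Discussion. It would not. The later visits belong to the treatment condition, and under Interventions TAU children who still meet PTSD criteria are offered the same therapy. The missing comparator limits that claim whatever recall period is used.

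It can also be said that this is a pilot with modest economic aims in its Health economics measures section, and that a uniform 3-month window keeps recall comparable between visits. The first point lowers the weight of the finding. But a study meant to test its resource-use instruments is the right place to settle the recall period before a larger trial inherits it. The second point is a real trade-off: nothing in the article shows how well minor contacts are remembered over 9 months. Recording the last 3 months separately keeps the comparable window.

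**Conclusion.** The point holds within limits. Under the stated schedule, service use is unobserved in months 3 to 9 after treatment: 6 of 12 post-treatment months, and 40% to 41% of the time from baseline to the last visit. This contradicts the aim of recording all use and weakens the 12-month cost description in treated children. It does not affect the between-arm cost comparison at post-treatment, provided treatment keeps to about 12 weeks as stated.

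The result rests on reading the follow-ups as counted from post-treatment, as Secondary clinical outcomes says, and on there being no other source of service-use data, since none is described. The Discussion sentence is too strong for two separate reasons: the recall gap and the lack of a randomised comparator after post-treatment. The recall change removes only the first. The finding is of moderate weight: worth correcting, with no threat to the primary clinical result.

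**What to change.** 1. At each post-baseline visit, ask about service use and work loss since the previous assessment. Keep the 3-month look-back at baseline. At post-treatment this changes almost nothing if treatment lasts 12 to 13 weeks, and it protects against an overrun.
2. At the 12-month visit, record the last 3 months separately from the 6 months before them. The planned 3-month data are then kept, and the two rates can be compared as a rough check on recall, although a real change in use could also make them differ.
3. Restate the Discussion sentence so that it claims preliminary cost-effectiveness at post-treatment and a descriptive 12-month cost profile in treated children.

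The cost is a reworded questionnaire, a few more minutes at one visit, and weaker recall of minor contacts in the older 6 months. Extra service-use contacts at 6 and 9 months with 3-month recall would also close the gap, with shorter recall but two more contacts per family. Neither route gives a randomised long-term cost comparison.

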### Blinding

Outcome assessments are conducted by independent raters from The Cambridge Centre for Affective Disorders (C2:AD) who have no therapeutic relationship with the patients and are blind to treatment condition. The independent raters are psychology graduates, post-doctoral psychologists and clinical psychologists. All have received additional training specifically in the use of the outcome assessments, the opportunity to listen to conducted assessments and have direct feedback on their assessments through supervision. Further to this, a randomly selected 20% of recordings will be reviewed by the lead developer of TF-CBT (PS).

Double-blinding of patients and therapists is not possible due to the nature of the trial (that is a psychological intervention). Under no circumstance will unblinding of patients or therapists be possible because they are not blind to intervention allocation.

### Statistical analysis plan

Initial analyses of the quantitative primary and secondary outcome data will be conducted on an intent-to-treat basis, with subsequent analyses being per protocol (based on attendance at 50% of offered sessions), and carried out by the trial statistician (PW) following CONSORT standards [33]. Comparisons will be made across groups on all outcome measures. For the continuous scales, repeated measures analyses of variance (ANOVAs) will be used without adjustment in the first instance, and then adjusting for baseline levels of the relevant measures as covariates if indicated. For the caseness measure of PTSD, non-parametric analyses will be used (for example, Chi square/Fisher’s exact test).

Qualitative interview data will be analysed using thematic analysis [34], facilitated by NVivo 8 software (QSR International). For the health economic data, mean estimated treatment costs in the two trial arms will be compared using ANOVA and the robustness of the parametric tests confirmed using bootstrapping. The primary analysis will explore cost-effectiveness in terms of loss of PTSD diagnosis (that is 'recovery'). If a significant difference in the primary outcome is observed between the two treatment arms, cost-effectiveness will be explored through calculation of an incremental cost-effectiveness ratio and sensitivity analyses.

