**Trial Consolidated Standards of Reporting Trials (CONSORT) diagram.**

### Interventions

TF-CBT-YC is a structured, manualised treatment, adapted from a treatment package developed for a previous trial of CBT for chronic PTSD (that is symptoms for > 6 months) in children and adolescents [18]. This treatment is based on a cognitive conceptualisation of PTSD [23,24] and specifically targets three maintaining factors of the disorder that are implicated in the aetiology of PTSD in youth: trauma memories, negative appraisals and maladaptive coping [23].

TF-CBT-YC is delivered to the child and parent or caregiver over 12 sessions of 60 to 90 minutes, supplemented by homework tasks. TF-CBT techniques for this age group have been derived both from our own published protocol for older children and adolescents developed for a previous trial [25], as well as the New Orleans protocol, used in the only published RCT for PTSD in this age group [17]. Treatment materials for this trial are developmentally sensitive with more complex cognitive exercises being introduced for the older children, as appropriate, in the 6 to 8 year age range. Specific techniques for the child and/or parent/caregiver include education about PTSD, recognition of feelings, training in coping skills, graduated exposure to the trauma through imagery, drawings and *in-vivo* work, the development of a coherent trauma narrative, the identification and reappraisal of erroneous trauma-related beliefs, and safety planning. Three sessions take place with the child and parent/caregiver together. The remaining sessions are divided into two halves. The first half involves the therapist and child only, but information is shared with the parent or caregiver via the therapist with the child’s knowledge. This facilitates parallel learning of the material and caregiver’s attunement to the child’s needs and feelings. The second half of each session involves just the therapist and parent or caregiver and provides a forum to discuss any problems, to assist the therapist in developing an understanding of the child’s behaviour outside of the session, and to plan and troubleshoot the homework assignments.

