Participants in the TAU arm do not initially receive any TF-CBT from the trial team. However, they are able to continue any therapeutic input they have already during this period, and any for which they are newly referred, and if at post-treatment assessment the child still meets criteria for PTSD, they are then offered TF-CBT-YC, exactly as described above.

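### At the post-treatment comparison the per-protocol attendance rule can remove children from the TF-CBT-YC arm only, so that contrast is not a randomised one and its bias has no known direction

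*Protocol article*

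**What the plan says.** Under Statistical analysis plan, the protocol article orders the analyses. The first step is fixed as follows: "Initial analyses of the quantitative primary and secondary outcome data will be conducted on an intent-to-treat basis". A second analysis set, defined by attendance alone, comes after it and is described as "per protocol (based on attendance at 50% of offered sessions"). On the scope of both, the article adds: "Comparisons will be made across groups on all outcome measures". No per-protocol criterion is given for TAU.

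Under Interventions, the active treatment has a fixed length: "TF-CBT-YC is delivered to the child and parent or caregiver over 12 sessions of 60 to 90 minutes". For the control arm, "Participants in the TAU arm do not initially receive any TF-CBT from the trial team". These children may receive other care: "they are able to continue any therapeutic input they have already during this period, and any for which they are newly referred". Trial treatment reaches them only after the primary endpoint: "if at post-treatment assessment the child still meets criteria for PTSD, they are then offered TF-CBT-YC".

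The primary outcome, under Primary clinical outcomes, is recovery from PTSD on the DIPA interview at post-treatment.

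**The concern.** A per-protocol set is meant to show what happens when treatment is taken as intended. Here the one criterion is attendance at trial sessions, and one of the two arms has none to attend before the endpoint. Families who attend poorly leave the TF-CBT-YC arm. Their counterparts in TAU, who would also have attended poorly, cannot be identified and stay in.

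Attendance is decided after randomisation and may well be related to family circumstances and to the child's symptom course. The balance sought by minimising on age group, gender and severity is then no longer protected. A difference between the remaining groups mixes any treatment effect with the difference between attenders and non-attenders.

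The stake is how the number might be used. Under Determination of sample size, the article says that the trial will give working knowledge of the likely effect size ahead of a larger evaluation. A per-protocol figure that looks like the effect in treated children could enter that planning, although the article does not say that it will.

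**Working it through.** **1. Can the rule act in both arms?** Set the passages side by side, at the post-treatment assessment:

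| | TF-CBT-YC | TAU |
|---|---|---|
| Trial sessions offered by then | course of 12 | none |
| Can a child fail the 50% rule? | yes | no, there is nothing to attend |
| Children in the per-protocol contrast | attenders only | everyone |

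So in the randomised comparison the rule selects in one arm. It can also apply to TAU children who take up TF-CBT-YC later, but those children enter only the pre- to post-treatment comparison, which has no concurrent control.

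**2. Inputs for an illustration.** From Determination of sample size: 45% recovery in TAU, 22 recruited per arm, one-sided 5% level. These figures are coherent. With 45% versus 89% and 17 per arm, the exact power of a one-sided Fisher test is 81.4%, against the stated 80%. And 17/0.80 = 21.25, which rounds up to 22. Assumed, because the document gives no figures: no true effect, so 45% in both arms; a share f = 0.20 of TF-CBT-YC children failing the rule; and a recovery rate q among those excluded, varied from 15% to 65%.

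**3. Formula.** Overall recovery in the TF-CBT-YC arm is a weighted mean of attenders and excluded children, so

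attender recovery = (0.45 - f × q) / (1 - f), and bias = attender recovery - 0.45.

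**4. Results with f = 0.20.** The last column is the probability that a one-sided Fisher test at 5% declares a benefit when there is none, found by enumerating 18 attenders (22 × 0.80 = 17.6, rounded) against 22 TAU children. For intent-to-treat with 22 against 22 it is 2.4%.

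| q | Attender recovery | Bias (points) | False-positive probability |
|---|---|---|---|
| 15% | (0.45 - 0.03)/0.80 = 52.5% | +7.5 | 6.9% |
| 25% | (0.45 - 0.05)/0.80 = 50.0% | +5.0 | 5.0% |
| 45% | (0.45 - 0.09)/0.80 = 45.0% | 0 | 2.5% |
| 65% | (0.45 - 0.13)/0.80 = 40.0% | -5.0 | 1.1% |

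With f = 0.30 and q = 15%, the attender rate is (0.45 - 0.045)/0.70 = 57.9%, a bias of +12.9 points. With f = 0.10 and q = 15%, it is (0.45 - 0.015)/0.90 = 48.3%, a bias of +3.3 points.

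**5. The randomisation-based alternative on the same inputs.** In every row the intent-to-treat difference is 45% - 45% = 0. If 80% of the TF-CBT-YC arm and nobody in TAU receive the treatment, the complier-average estimate is 0/(0.80 - 0) = 0, whatever q is. In general, with those shares, it is the intent-to-treat difference times 1/0.80 = 1.25.

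**6. The session count.** Against the 12 planned sessions the threshold is 0.5 × 12 = 6. If only sessions offered before a family stopped were counted, 2 of 4 or 1 of 2 would pass. The article does not say which is meant.

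**The case against.** Several counter-arguments have weight. Intent-to-treat comes first, and the per-protocol analyses are expressly subsequent, so the main result does not depend on this rule. That stands, and it limits the point to the later analyses. Selection after randomisation affects every per-protocol analysis, and one-sided attendance comes with comparing a therapy with TAU. That is also true, but it explains the problem without removing it: the article states this rule and says that groups will be compared.

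The size rests on assumed inputs. That is right too. Families may stop because the child is better as well as because things go badly, so the bias may be zero or negative. It is also small beside sampling error. With 18 against 22 children at 45%, the standard error of the difference is √(0.45 × 0.55 × (1/18 + 1/22)) = 0.158, about 16 points, and the trial is planned around a difference of 44 points.

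A reader might infer from the word *offered* that the denominator shrinks when a family drops out, so that one session out of two would count as adequate treatment. The document does not support that as a finding. The course is set at 12 sessions, and a family that withdraws early may still be said to have been offered all 12. The word is ambiguous, no more, and a fuller plan may define it.

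Finally, the complier-average effect has assumptions of its own. Those are real and are dealt with under the fix.

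**Conclusion.** The point holds for the randomised post-treatment comparison. The only stated per-protocol criterion can exclude TF-CBT-YC children and no TAU children, so the between-arm contrast compares a selected group with an unselected one. With 20% excluded, no true effect and 45% recovery in both arms, the bias runs from +7.5 points (those excluded recover at 15%) through 0 (at 45%) to -5 (at 65%). Of these inputs only the 45% TAU rate is the document's own. Neither the direction nor the size can be known beforehand, and that is the reason not to rely on the contrast.

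Two stronger readings should be resisted. The documents do not show that the rule favours TF-CBT-YC, because that depends on who stops attending and why. Nor do they show that the trial's main conclusion is at risk, because the intent-to-treat analysis is untouched. The change is worth making because it is cheap and because this trial prepares a larger one.

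**What to change.** For the between-arm effect in treated children, replace the per-protocol contrast, or accompany it, with a complier-average causal effect that uses randomisation as the instrument:

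intent-to-treat risk difference / (share receiving treatment in TF-CBT-YC - share receiving equivalent TF-CBT in TAU), with a bootstrap confidence interval.

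- Define receipt as at least 6 of the 12 planned sessions, which also settles what *offered* means.
- That threshold assumes that attending fewer than 6 sessions has no effect. If partial attendance helps, the estimate is too large. Repeat the analysis with receipt defined as any session attended.
- Count any equivalent TF-CBT obtained outside the trial in the TAU share, since TAU children may continue existing therapy or start newly referred therapy.
- Label any per-protocol contrast that remains as supportive and non-randomised. The attendance rule can stay for the uncontrolled pre- to post-treatment comparison.

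The cost is a few sentences of analysis wording, a few lines of code and a record of outside TF-CBT in TAU. The downsides are a wider interval than that of the simple per-protocol contrast, and reliance on the exclusion restriction, meaning that allocation affects recovery only through receipt of treatment as defined.
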